## Discussion

3

Currently, interventions for perinatal maternal depression can be divided into preventive and therapeutic interventions. Preventive interventions primarily focus on psychological interventions and are implemented for pregnant women showing signs of depression or at risk of depression; for those diagnosed with depression, a combination of drug and psychological therapy is used (69). Several studies have shown that drug therapy may have adverse effect on the neurological, behavioral, cognitive and emotional development of the fetus (70, 71). Thus, psychological interventions play a crucial role in the prevention and treatment of postpartum depression (72). Commonly supported theoretical interventions for maternal depression include positive thinking interventions (mindfulness-based interventions, MBI), cognitive behavioral therapy (CBT), and interpersonal therapy (IPT). Intervention channels based on mobile health, such as WeChat groups, hospital WeChat public accounts, and specially developed applications or websites, have become important platforms for communication between pregnant women and maternal and child health personnel (73). With these platforms, researchers can follow up with pregnant women, providing them with maternal and child health information during pregnancy and childbirth. This proactive approach has shown promise in preventing postpartum depression. However, most of the interventions are passively received by the mothers, with limited active feedback or output from them. In some cases, pregnant women’ feedback is limited to simple actions such as clicking links or filling out questionnaires, making it difficult to fully support pregnant women with depressive tendencies in expressing their emotions, thus limiting the effectiveness of interventions in improving maternal depression and enhancing their acceptance. A meta-analysis demonstrated the short-term efficacy of mindfulness-based interventions (MBI) during pregnancy for postpartum depression (PPD), but long-term outcomes remain unclear (74).

Compared with other similar interventions that include family support, this study focuses on a new, personalized behavioral intervention to reduce the risk of depression occurrence and further deterioration among pregnant women in China. The innovation of this mobile device-based intervention lies in retaining traditional nursing interventions, such as regularly delivering perinatal health knowledge to pregnant women, while also requiring pregnant women and their companions to actively record and share short videos of their experiences, thereby achieving a bidirectional interactive intervention. This intervention not only strengthens the effect of reducing depression symptoms among pregnant and puerperal women through companion-supported nursing but also shares records of different intervention themes in video form. This enhances feedback from pregnant and puerperal women to the research team and promotes interaction between them, thereby ensuring the effectiveness of the intervention. Therefore, family-supported companion video sharing may become a more effective strategy for alleviating depression among pregnant and puerperal women. This novel approach can provide preliminary evidence for the reduction of adverse psychological symptoms, such as depression, among pregnant women, as well as the long-term effects of such interventions.

This study involves the use of smart devices and the cooperation of caregivers. The research team believes that pregnant women may encounter the following situations when facing new interventions: 1) low acceptance of emerging things (such as mobile health strategies and video sharing formats); 2) concerns about personal privacy leakage, as the video content involves the recent lives of pregnant women and their partners; 3) insufficient cooperation from caregivers, as some caregivers may prefer traditional intervention and care models due to a lack of knowledge and experience related to accompanying pregnant women, leading to concerns about new interventions. In response to the above situations, the research team will present the latest research results on improving maternal depression through mobile health strategies to pregnant women and their caregivers during the initial recruitment phase, and explain that this study provides free professional clinical assessment and consultation services to pregnant women throughout the entire pregnancy. Pregnant women and caregivers who are screened will receive a one-on-one explanation of the requirements for video shooting during the start of the study to ensure the quality of the accompanying videos. Pregnant women and caregivers will be informed that the videos are managed by dedicated research assistants from the research team and that privacy will not be leaked, thereby alleviating their concerns. Additionally, there are a few limitations to this study, such as a small sample size, a single-center study, and variations in caregiver participation levels. Furthermore, this study only follows up to four weeks postpartum, which makes it hard to see the long-term effects on postpartum depression. To tackle the issues with how widely the results can be applied due to the small sample size and single-center trial, specific details about the intervention have been provided as **Supplementary Material** to ensure the reproducibility of the intervention measures. Future research is recommended to extend the follow-up period to look into how the intervention affects postpartum depression over time.

The results of this study will provide scientific evidence advocating for wider promotion and application of mobile health interventions to prevent and address health issues of pregnant and postpartum women during the peripartum period. By demonstrating the benefits of family support–based mobile companion video sharing—that is, sharing supportive videos via mobile devices among family members—this study may serve as a reference for medical policies and practices. This, in turn, can ultimately improve maternal care and outcomes. Moreover, this research is expected to pave the way for further studies and innovations utilizing digital technology to support the health of pregnant and postpartum women. It also encourages interdisciplinary collaboration among healthcare providers, technology experts, and policymakers, to optimize peripartum care services. Overall, investing in mobile health intervention research for managing peripartum mental health has great potential to enhance the well-being of pregnant women and promote maternal and infant health outcomes.

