**Methods:**

The study involves 40 pregnant women with mild to moderate depression symptoms and conducts an eight-month randomized controlled trial. Participants are randomly assigned to the intervention or control group. The intervention group receives a mHealth intervention involving six weeks of themed video sharing with their caregivers, based on mindfulness theory. Participants are required to record and share videos with their caregivers via WeChat according to weekly themes, in collaboration with the research team. The research team also regularly sends healthcare messages, creating a bidirectional intervention. The control group only receives healthcare messages. All participants are required to complete five follow-up visits, with depression levels assessed using the 5-item short form of the EPDS (EPDS-Dep-5).

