Mobile Health (mHealth) has garnered attention as a promising avenue, with the World Health Organization (WHO) actively promotes adopting digital technologies to improve various patient care models (24–28). mHealth apps play a pivotal role in patient education, disease self-management, remote patient monitoring, and overall improvement of quality of life (29–31). For instance, the Interactive Maternal Information and Emotional Support Group (IMAGINE) demonstrated improved emotional management and acceptance of mental health care. This was achieved through personalized communication with guidance specialists and peer support (32). Similarly, a Japanese mHealth-based randomized controlled trial (RCT) showcased the preventive impact of a mobile health counseling app on postpartum depressive symptoms (33). Studies on Positive Thinking-Based Interventions (MBIs) have highlighted the efficacy of digitally guided self-help interventions in alleviating maternal depression throughout the perinatal period, with mHealth-based interventions exhibiting lower dropout rates and greater acceptability compared to face-to-face interventions (34–36). These interventions use various mHealth platforms to deliver support, such as online support groups, email or text messaging, mobile apps, and web pages (32, 33, 37–40). Despite the widespread use of mHealth, its effectiveness in reducing perinatal depression or anxiety remains inconclusive, with only a few apps being considered high quality (41, 42). Therefore, there is a critical need for the development of high-quality mHealth apps and rigorous evaluation of their potential to improve perinatal maternal mental health. This field warrants further research and investment to provide effective and accessible support for pregnant women experiencing depression and anxiety.

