### Recruitment

2.3

We began recruiting perinatal pregnant women on August 12, 2024 using a multi-channel approach. This approach encompassed online platforms, hospital settings, and community outreach. Initially, announcements related to the trial were shared through the WeChat public account of Dongying People’s Hospital and its affiliated medical institutions, providing links to an electronic questionnaire for interested perinatal mothers and their companions to submit their contact information. Additionally, medical staff at the Obstetrics and Gynecology Specialist Outpatient Clinic of Dongying People’s Hospital inform perinatal pregnant women attending appointments about the study and provide questionnaires to those interested or showing signs of depression. Moreover, community health workers at various health service centers in urban areas associated with Dongying People’s Hospital promote the study and enroll eligible participants by administering questionnaires.

After identifying interested individuals who met the inclusion criteria, researchers clarified the study’s objectives and procedures. Then, the study’s medical personnel meticulously screened and selected eligible perinatal women based on predefined criteria. Each participant received a detailed letter of informed consent (refer to Appendix), detailing the study’s aims, procedures, and potential implications. After both parties mutually agreed and signed the informed consent, the participants who completed this process formed the recruited cohort. Random allocation then determined the assignment of participants to either the intervention group (companion video-sharing group) or the control group (traditional care group).

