### Randomization

2.6

Following the baseline study visit, all participants were randomly assigned to one of the two study groups using a 1:1 randomization method. The randomization process involved using a random number table method.

Here’s the specific randomization process:

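### Before allocation, recruits are to be shown research on mobile health improving maternal depression; with recognisable arms and a self-rated outcome, this adds an avoidable expectation risk of unknown size

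*Protocol article*

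**What the plan says.** The protocol article's Discussion (Section 3) lists acceptance problems the team expects: reluctance towards mobile health and video formats, privacy worries, and caregivers who favour conventional care. In response, the team plans to "present the latest research results on improving maternal depression through mobile health strategies to pregnant women and their caregivers during the initial recruitment phase". The next step, timed at the study's start, is stated as "Pregnant women and caregivers who are screened will receive a one-on-one explanation of the requirements for video shooting", and its purpose is "to ensure the quality of the accompanying videos". Neither sentence names an arm.

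On order, Section 2.3 (Recruitment) describes screening and consent and continues: "Random allocation then determined the assignment of participants to either the intervention group". Section 2.6 (Randomization) adds: "Following the baseline study visit, all participants were randomly assigned to one of the two study groups using a 1:1 randomization method".

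On the evidence for mobile health in this field, the Background (Section 1) says that "its effectiveness in reducing perinatal depression or anxiety remains inconclusive".

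On the comparator, the abstract's Methods paragraph says: "The control group only receives healthcare messages". Section 2.9 describes these as weekly texts or images sent by WeChat for six weeks. The video arm has nurse teaching, filming and a weekly online exchange (Section 2.7).

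On measurement, the primary outcome is EPDS-Dep-5 (Section 2.10.1), and participants fill in the questionnaires themselves online (Section 2.13.1). The only statement on blinding concerns the monitoring committee (Section 2.16). The limitations in Section 3 are sample size, single centre, varying caregiver involvement and short follow-up. They mention neither expectation nor participants' knowledge of their arm.

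**The concern.** The presentation is described as a way to raise acceptance, so its purpose is persuasive, and it comes before anyone knows her arm. A woman who has heard about mobile health improving depression and is then allocated to video may rate herself better out of hope. A woman who heard the same and is allocated to usual messages may rate herself worse out of disappointment. Both move the between-arm difference in favour of the intervention without any true effect, and the trial has no blinded or objective measure of mood to set against the self-rating.

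Participants in a trial of this kind cannot be blinded. A non-neutral message before allocation, however, is a choice that can be changed. The filming briefing raises a smaller, separate matter. If it really goes to all screened dyads, women who will become controls are prepared for an activity they are then not offered. That could add to disappointment or, in the other direction, prompt some of them to film on their own.

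**Working it through.** **Sequence, as the sections give it**

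1. Recruitment: research results on mobile health are presented (Section 3).
2. Screening and consent (Section 2.3).
3. Start of study: filming briefing for screened dyads (Section 3). Its position relative to allocation is not stated.
4. Baseline visit, then allocation by envelope (Section 2.6).
5. Six weeks of recognisably different care (Sections 2.7 and 2.9).
6. Self-completed EPDS-Dep-5 at each visit (Sections 2.11 and 2.13.1).

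Step 1 reaches both future arms equally, so on its own it creates no difference. A difference can arise only from step 5, when what a woman was led to expect meets what she received.

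**Can a size be derived?** No. The documents give neither a reporting shift nor an SD for EPDS-Dep-5. The only SDs are 2.4 and 1.4 in Section 2.5, and they accompany EPDS means of 12.0 and 14.9. EPDS-Dep-5 has five items scored 0 to 3, so its maximum is 15; the full scale's is 30.

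**Check of method on the plan's own figure.** Welch t-test, 20 per arm, difference 2.9, SDs 2.4 and 1.4:

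- SE = √(2.4²/20 + 1.4²/20) = √0.386 = 0.621
- noncentrality = 2.9/0.621 = 4.67, Satterthwaite df about 30.6
- power = 99.472%, as stated in Section 2.5. The inflation 32/(1 − 0.2) = 40 also agrees.

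**Illustration under assumptions.** True effect zero; 16 analysed per arm (Section 2.5 before attrition); two-sided 5% t-test, df = 30; total between-arm reporting shift b; common SD s. Noncentrality = b/(s·√(2/16)) = b/(0.354·s).

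| Assumed SD | b = 0.5: noncentrality, rejection rate | b = 1.0: noncentrality, rejection rate |
|---|---|---|
| 2.0 | 0.71, 10.5% | 1.41, 27.8% |
| 2.5 | 0.57, 8.5% | 1.13, 19.5% |
| 3.0 | 0.47, 7.4% | 0.94, 15.0% |

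With the protocol's full-scale SDs (2.4 and 1.4) and a Welch test at 16 per arm, shifts of 0.25, 0.5 and 1.0 give 6.4%, 10.6% and 28.2%. These SDs belong to a different scale, so the figures do not carry over directly.

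The table shows only that a reporting shift of half a point to one point would matter in a trial of 40. It does not show that such a shift will occur.

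**Filming briefing.** The wording names dyads who are screened. The stated purpose, video quality, concerns only dyads who will film, and controls make no videos. The recipient and the purpose therefore do not match, and the timing does not settle which is meant.

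**The case against.** The strongest reply is that the text shows less than it seems to. Several stronger readings are tempting, and the documents do not support them.

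- *Women are told that companion video sharing works.* The article says that research results on mobile health will be presented. No script is shown, the content is not known, and Section 2.3 says only that researchers explained objectives and procedures. Recent results could be shown in a balanced way, so a direct contradiction with the Background is not established; the two fit poorly as worded.
- *Consent rests on a one-sided account.* The consent letter is in an appendix that is not available here, so nothing can be said about it.
- *The fault is that the message is not limited to the intervention arm.* This is backwards. Giving the message to one arm only would worsen expectation bias. The fault is non-neutral content before allocation.
- *Controls are taught the intervention.* Hearing the requirements for filming is not six weeks of nurse-led themes, filming, feedback and exchange.
- *The false-positive rate is a particular figure.* Nothing in the documents anchors the shift. The calculation also uses a t-test on completers, while Section 2.12 plans GEE with multiple imputation.

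It is also fair to say that controls receive WeChat materials, so a general message about mobile health separates the arms less sharply, and that the filming briefing is naturally read as meant for dyads who will film.

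What stands after this: a stated procedure aimed at raising acceptance, placed before allocation, in a trial with recognisable arms and a self-rated primary outcome, and with no mention of the risk among the limitations.

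**Conclusion.** The point holds as an avoidable risk, not as a demonstrated bias. The recruitment presentation can add hope in the video arm and disappointment in the control arm to the EPDS-Dep-5 ratings once allocation is known. The likely direction favours the intervention. The size cannot be estimated from the documents, and the percentages above rest wholly on assumed shifts and SDs. Any unprompted filming by controls would work the other way.

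That participants are unblinded is inferred from the difference between the arms; the article does not use the term open-label. The filming briefing is a matter of wording: as written it reaches screened dyads, and its purpose suggests a narrower group. Overall this is a cheap improvement and does not threaten the design.

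**What to change.** In the Discussion paragraph on expected acceptance problems, and in the recruitment material it describes:

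1. Replace the presentation of results with neutral information, identical for all women and caregivers: the effect of companion video sharing is not known, and both groups receive health information.
2. State that the one-on-one filming briefing takes place after the envelope is opened, for the intervention arm only, and makes no claims about efficacy.
3. Add to the limitations that participants are not blinded and the primary outcome is self-reported. For women already recruited, disclose there what they were told.

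The cost is an ethics notification and possibly a slightly lower consent rate without the persuasive message. Sample size, visits and analysis do not change.
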